### Interventions

In the nutritional intervention, men are randomised to either a lycopene supplement intervention or a plant-based intervention or a nutritional control arm. The lycopene intervention involves one 10 mg lycopene capsule daily (provided to the man). The plant-based intervention comprises eating as many portions of fruit and vegetables daily as possible, aiming for at least five portions, and swapping dairy milk for non-dairy alternatives, for example, soya milk, as often as the men can. The control arm men carry on with their usual diet; if the men ask for nutritional advice, standard, publically available, information is provided.

In the physical activity intervention, men are randomised to either walking at a brisk pace for 30 minutes, on at least five days a week, on top of their usual physical activity or to continue with their usual levels of physical activity.

The men are provided with materials and detailed instructions specific to their allocated intervention arm by trained research nurses and asked to follow their allocated intervention arm for 6 months.

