### Primary outcome measures

Co-primary outcomes are randomisation rates (the proportion of eligible men who agree to be randomised) where a rate of 65 % or above would be considered acceptable [33] and adherence to the interventions at 6 months following randomisation, where a rate of 75 % or above would be considered acceptable. Adherence will be calculated for both the nutrition and physical activity interventions and is taken to be following intervention instructions > 90 % of the time. Adherence to the nutrition intervention will be assessed by participant self-report on the daily monitoring form. This form is completed daily by the participants for the duration of the 6-month intervention. For the lycopene arm, men are asked if they took their supplement daily - yes/no; for vegetable and fruit consumption, men are asked how many portions they consumed daily; for dairy milk consumption, men are asked how much of their dairy milk they replaced with an alternative – all/some/none. Adherence to the physical activity intervention will be assessed by their self-reported adherence to the recommended minimum 30 minutes of brisk walking five times per week during the 6-month intervention phase.

In order to assess the adherence rate with a confidence interval of ± 5 % and an estimated expected adherence rate of 75 %, the required minimum sample size for this feasibility study would be approximately 75 participants [34]. Incorporating an expected randomisation rate of 80 %, we intend to recruit at least 100 men into this study.

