### Analysis plan

The primary comparative analyses will be by intention-to-treat. Baseline characteristics of each group will be tabulated using means and standard deviations for normally distributed data, medians and interquartile ranges for non-normally distributed data, and percentages and counts for categorical data. Randomisation rate and adherence to the intervention will both be reported as a percentage, along with the respective 95 % confidence interval.

We will also conduct exploratory analyses of change in physical activity and fruit and vegetable consumption (as measured for adherence to the interventions) will be analysed using a two-way ANOVAs or appropriate non-parametric tests if necessary. Change in selected secondary outcomes (IGF-I, PSA and blood biomarkers) will be analysed similarly, although this study is not powered for secondary outcomes. These analyses will focus on the main effects of the interventions, but we will also explore possible interactions between the interventions with respect to these outcomes. Assuming 80 men are recruited into the trial, this will provide approximately 90 % power to detect a large main effect size (f = 0.4) with an alpha level of 0.05, analysing the study as a 2 x 3 factorial design (power will be reduced after correcting for multiple testing). We will also explore associations between baseline Stage of Change; behavioural, normative and control beliefs; and adherence to the interventions using chi-square tests and logistic regression models.

Qualitative data collected during this research will be analysed thematically using a qualitative method, such as the framework approach [38]. Individuals will not be identified by name in the written transcript. A qualitative analysis computer programme, such as NVivo [39], will be used to assist analysis.

The SPIRIT 2013 checklist [40] and the CONSORT statement [41] were followed and adhered to during the development of the trial protocol and implementation. The PrEvENT trial has been given full ethical approval by Cornwall and Plymouth Research Ethics Committee (REC), ref: 14/SW/0056, and registered on the ISRCTN registry, ref number ISRCTN99048944. All participants provide fully informed consent.

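### The ±5% precision for adherence is worked out on all randomised men, but each adherence rate as defined rests only on the men allocated to that active intervention, and none of these rates reaches ±5%.

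*Protocol article*

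**What the plan says.** Under Primary outcome measures, the protocol article makes adherence at 6 months a co-primary outcome, with 75% or above counted as acceptable. The sample size rests on it: "In order to assess the adherence rate with a confidence interval of ± 5" per cent and "an estimated expected adherence rate of 75" per cent, "the required minimum sample size for this feasibility study would be approximately 75 participants". The next step is "Incorporating an expected randomisation rate of 80 %, we intend to recruit at least 100 men into this study". Recruitment into the randomised control trial gives the matching target of at least 80 men randomised.

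The same section states that "Adherence will be calculated for both the nutrition and physical activity interventions". The measures it then describes are whether the lycopene supplement was taken, portions of fruit and vegetables, replacement of dairy milk, and the recommended minimum of brisk walking.

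Under Interventions, the comparison conditions are usual behaviour. For nutrition, "The control arm men carry on with their usual diet"; for physical activity, men are allocated to brisk walking "or to continue with their usual levels of physical activity". The Analysis plan reports adherence as a percentage "along with the respective 95 % confidence interval".

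**The concern.** The only scaling between the 75 men and the 100 to be recruited is the randomisation rate. Nothing allows for the 2 x 3 factorial split, so the 75 are men from all six cells. The outcome as described, however, is at least two rates, each with a measure that has content only for men given that active intervention. The denominator in the sample size is therefore not the denominator of either rate.

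Adherence is co-primary, and its result is meant to inform a larger trial. A reader who takes the sample-size sentence at face value would expect an observed 75% to be known to within about 70% to 80%. Correcting only the confidence multiplier, and keeping 75 as the denominator, would still credit each rate with more precision than it has.

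**Working it through.** **Inputs.** Expected adherence p = 0.75, precision ±0.05, about 75 men, randomisation rate 80% and at least 100 recruited (Primary outcome measures); at least 80 randomised (Recruitment into the randomised control trial); 2 x 3 factorial (Trial setting and participants); 95% intervals (Analysis plan).

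**Assumptions.** The article gives no allocation ratio, so equal allocation is assumed: 1/2 of the men to walking, 2/3 to an active nutrition arm, 1/3 to each single nutrition arm. No loss by 6 months is assumed.

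**The plan's own figure.** For a 95% half-width of 0.05:

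n = 1.96² × 0.75 × 0.25 / 0.05² = 288.1, so 289 men, not 75.

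Two unstated routes lead to about 75:

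- ±5% as one standard error: 0.75 × 0.25 / 0.05² = 75.0.
- A finite-population correction that treats the 100 cohort men as the whole population: 288.1 / (1 + 287.1/100) = 74.4.

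The step to 100 is consistent with counting all randomised men: 75/0.8 = 93.75, and 80/0.8 = 100.

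**Precision by denominator.** SE = √(0.75 × 0.25 / n); 95% half-width = 1.96 × SE.

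| Rate | Men (of 80 randomised) | SE, points | 95% half-width, points | Exact 95% interval near 75% |
|---|---|---|---|---|
| All randomised men | 80 | 4.8 | 9.5 | 64% to 84% (60/80) |
| Walking | 80 × 1/2 = 40 | 6.8 | 13.4 | 59% to 87% (30/40) |
| Nutrition, both active arms | 80 × 2/3 ≈ 53 | 5.9 | 11.7 | 62% to 86% (40/53) |
| One nutrition arm | 80 × 1/3 ≈ 27 | 8.3 | 16.3 | 54% to 89% (20/27) |

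With the stated minimum of 75 randomised, all 75 men give 1.96 × 5.0 = ±9.8. Walking has 37.5 men (±13.9), pooled nutrition 50 (±12.0) and one nutrition arm 25 (±17.0).

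**Does either route to 75 rescue the per-intervention rates?**

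- One standard error: the SEs are 6.8, 5.9 and 8.3 points, all above 5.
- Finite-population correction to 100 men: walking 13.4 × √(60/99) = 10.4; nutrition 11.7 × √(47/99) = 8.0. If the population is also split, to 50 and 67 men, walking gives 13.4 × √(10/49) = 6.1 and nutrition 11.7 × √(14/66) = 5.4. All exceed 5.

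**Sensitivity to the allocation ratio.** No split of 80 men puts 289 in a denominator. On the one-standard-error reading, a rate needs 75 men, which would leave at most 5 of 80 as controls for that factor.

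**The case against.** The strongest objection is that control men do have something to follow. Interventions says that the men receive instructions specific to their allocated arm and are asked to follow that arm for 6 months, with no exception for controls. The Summary speaks of adherence to the intervention arm in general. One could therefore count all randomised men, with carrying on as usual treated as adherence. A reader might infer from this review that controls were given no instruction at all; the text does not support that. What stands is narrower: no adherence measure is defined for controls. A rate that included them would say little about whether men take up the interventions, and at 80 men it would still have a 95% half-width of ±9.5.

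Second, 40 and 53 are not the only possible denominators. The sample-size sentence speaks of a single rate. One rate over men with any active allocation would cover 5 of 6 cells: 80 × 5/6 ≈ 67 men, SE 5.3, about ±10.4. In the other direction, lycopene and the plant-based diet are measured differently, and separate rates would rest on about 27 men each. Pooling them into 53 is a choice. This objection is right about the figures, but no option gives ±5.

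Third, the method comes from a cited source that is not at hand, so neither derivation of 75 can be confirmed. That is accepted; the conclusion holds under both.

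Fourth, the practical effect is limited. The 75% mark is a rate with no rule on a confidence limit, and the reported intervals will show the precision achieved. This is fair, and it is why the remedy is a restatement only.

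**Conclusion.** The point holds. The article states a precision for a co-primary outcome on a denominator that its own definition of adherence does not use. With 80 randomised, equal allocation and no loss by 6 months, expected 95% half-widths are about ±13 points for walking, ±12 for pooled nutrition and ±16 for a single nutrition arm, against the stated ±5.

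Two faults combine. The 95% multiplier alone takes 75 men to ±9.8; the denominator takes the rates from there to ±12 or more. The second fault remains on the one-standard-error reading.

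The individual figures depend on an unstated allocation ratio and on pooling. Any loss by 6 months would make them worse unless men lost are counted as non-adherent. The conclusion that ±5% is not met does not depend on those choices. A reader might go further and infer that the trial is too small or that its acceptability mark is invalid. The document does not support that: this is a feasibility trial, and no decision rule is tied to the width of the interval.

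**What to change.** Keep the planned numbers. In Primary outcome measures:

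- Delete the statement that about 75 randomised men give ±5% for adherence.
- Name the denominator of each adherence rate as the men allocated to that active intervention, and say whether lycopene and the plant-based arm are pooled or reported separately.
- Restate the expected 95% precision for each rate with its assumptions. For example: with 80 randomised in equal allocation, 75% adherence and no loss by 6 months, about 40 men and ±13 points for walking; about 53 men and ±12 points for nutrition if the two active arms are pooled; about 27 men and ±16 points for each if they are not. If the true allocation ratio differs, recompute.
- Say how men lost before 6 months enter the denominator.

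This is a change of wording. It needs no extra men, and its cost is a less favourable stated precision.

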### Secondary outcome measures

The secondary outcomes include intervention tolerability (based on qualitative interviews and reported adverse events), retention (men successfully followed up at 6 months, as a proportion of those who were recruited to the trial and randomised into a study arm), change in PSA (a protein produced by cells of the prostate gland, which is often elevated in men with prostate cancer) [35] and insulin-like growth factor (IGF-I) levels (raised IGF-I levels are increasingly being implicated as a potential risk factor for cancer) [36] and change in all other data collected between intervention groups at the different time points. We will explore whether biomarkers of lycopene for the lycopene intervention arm, alpha-carotene, beta-carotene, lutein, lycopene, total carotenoids and vitamin C for fruit and vegetable intake, and phyto-oestrogen, as a biomarker for soya milk, are affected by the proposed interventions. Full details of the data being collected at specific time points are described in Table 2. The study was not powered for secondary outcomes.

### Tissue collection

All samples are collected, used and stored in accordance with the Human Tissue Act 2004. Prostate tissue sections are formalin-fixed and tissue that is surplus to diagnostic requirements is stored for later analysis of nutritional and physical activity biomarkers (including epigenetic and metabolomic biomarkers) and surrogate biomarkers of prostate cancer (for example, expression levels of IGF-I). Stage, margin status and Gleason score for each radical prostatectomy specimen will be recorded. Collection of blood samples will allow biological mechanisms linking nutritional, physical activity and other lifestyle factors with prostate cancer risk and progression to be further investigated.

### Theoretical underpinning

Three psychological theories will be employed during the PrEvENT trial, each serving a unique purpose. These are ‘Teachable Moments’ [5], the Transtheoretical Model of Change (Stages of Change) [37] and the Theory of Planned Behaviour [32].

Data analysis will allow exploration of whether men with prostate cancer make naturally occurring changes to their diet and physical activity as a result of their cancer diagnosis and treatment. This will assist in establishing whether receiving a diagnosis of prostate cancer and undergoing treatment can be utilised as a ‘Teachable Moment’ [5]. It is hypothesised that prostate cancer diagnosis is a health event, or Teachable Moment, thought to motivate individuals to make changes to health or lifestyle behaviour.

The Transtheoretical Model of Change (Stages of Change) [37], assesses an individual’s level of readiness to change. The model categorises people into a number of stages. Men in the trial will have their readiness to change assessed at the four data collection time points. Analysis will then establish whether men, at different levels of readiness to change, respond differently to the intervention. Additionally, it will be established whether the men’s level of readiness to change alters during the trial.

The Theory of Planned Behaviour [32] explores three key considerations which are proposed to influence whether an individual will make a behaviour change or not. These are behavioural beliefs, normative beliefs and control beliefs, which combine to influence intention to change behaviour. The PrEvENT trial participant-facing documents have been developed in a manner that intends to influence these three theoretical considerations, thus helping to implement the behaviour change in the men, and improve adherence and acceptability of the interventions.

### Analysis plan

The primary comparative analyses will be by intention-to-treat. Baseline characteristics of each group will be tabulated using means and standard deviations for normally distributed data, medians and interquartile ranges for non-normally distributed data, and percentages and counts for categorical data. Randomisation rate and adherence to the intervention will both be reported as a percentage, along with the respective 95 % confidence interval.

We will also conduct exploratory analyses of change in physical activity and fruit and vegetable consumption (as measured for adherence to the interventions) will be analysed using a two-way ANOVAs or appropriate non-parametric tests if necessary. Change in selected secondary outcomes (IGF-I, PSA and blood biomarkers) will be analysed similarly, although this study is not powered for secondary outcomes. These analyses will focus on the main effects of the interventions, but we will also explore possible interactions between the interventions with respect to these outcomes. Assuming 80 men are recruited into the trial, this will provide approximately 90 % power to detect a large main effect size (f = 0.4) with an alpha level of 0.05, analysing the study as a 2 x 3 factorial design (power will be reduced after correcting for multiple testing). We will also explore associations between baseline Stage of Change; behavioural, normative and control beliefs; and adherence to the interventions using chi-square tests and logistic regression models.

Qualitative data collected during this research will be analysed thematically using a qualitative method, such as the framework approach [38]. Individuals will not be identified by name in the written transcript. A qualitative analysis computer programme, such as NVivo [39], will be used to assist analysis.

The SPIRIT 2013 checklist [40] and the CONSORT statement [41] were followed and adhered to during the development of the trial protocol and implementation. The PrEvENT trial has been given full ethical approval by Cornwall and Plymouth Research Ethics Committee (REC), ref: 14/SW/0056, and registered on the ISRCTN registry, ref number ISRCTN99048944. All participants provide fully informed consent.

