### Initial recruitment phase

Men are recruited to the trial via a consecutive opportunistic sample; that is, men who are conveniently accessible to the research team in the urology outpatients clinic and who meet the inclusion criteria are invited to participate until the sample size is reached and then are introduced to the study by a member of the clinical care team at the appointment where a decision about treatment is made. The expected duration between the appointment where a decision about treatment is made and surgery is approximately 4 weeks. Men who indicate an interest in the trial are directed to the research nurse for further information and given an initial research appointment where informed consent into the cohort is obtained and key data collected. Data that are obtained include i) a baseline questionnaire, including collection of information about diet, physical activity levels, mood and prostate symptoms and ii) blood samples used to assess baseline levels of nutritional biomarkers and biomarkers of prostate cancer progression, such as PSA. Men who consent will allow prostate tissue samples to be obtained from the prostate that is removed at surgery. The tissue is stored for future analysis. Full details of data collected at each time point can be found in Table 2. Each man’s National Health Service (NHS) number is also recorded for anonymous data linkage to routine NHS electronic datasets, such as the Cancer Registries and the Office for National Statistics Vital Statistics dataset. Recruitment into the cohort study will continue until the specified sample size (n = 100) has been reached.

**Table 2 Tab2:** Data collected during PrEvENT

Participant assessment	Who					When							
	Usual care team	Consultant	Research nurse	Participant	Research team	Pre-screening	Cohort baseline appointment	Surgery	Cohort follow-up/true trial baseline appointment	6-month intervention duration	3-month follow-up appointment	6-month follow-up appointment	Evaluation interview
Eligibility screening	X	X	X			X							
Informed consent			X	X			X		X				
Demographic data				X			X		X		X	X	
Family medical history				X			X		X		X	X	
Anthropometric data weight, height, % body fat			X				X		X		X	X	
Blood sample			X				X		X			X	
Diet data FFQ [43]				X			X		X		X	X	
Physical activity data Recent Physical Activity Questionnaire [44]				X			X		X		X	X	
Urinary symptoms ICSmale-SF [45]				X			X		X		X	X	

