Psychological measures POMS-SF [46] and Benefit Finding Scale [47]				X			X		X		X	X	
Health beliefs data Adapted from [37] and [32]				X			X		X		X	X	
Quality of life measures FACT-P [48]				X			X		X		X	X	
General health data SF-12 [49]				X			X		X		X	X	
Cancer related fatigue FACIT-Fatigue [48]				X			X		X		X	X	
Lifestyle data Drinking and smoking				X			X		X		X	X	
Accelerometry data				X			X		X			X	
Prostate tissue		X						X					
Pedometer data				X						X			
Daily monitoring data Step count, record of fruit, vegetable, dairy and lycopene intake				X						X			
Qualitative evaluation data				X	X								X

At 5 weeks post-surgery, all men are posted a follow-up data collection questionnaire and invited to a second appointment with the research nurse.

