### Recruitment into the randomised control trial

Men invited to participate in the RCT will have agreed to be contacted about further related research during the initial cohort recruitment phase. Along with the post-surgery follow-up data collection questionnaire, these men receive an invitation to participate in the RCT. They are telephoned by the research nurse and screened for trial eligibility. Inclusion and exclusion criteria for the RCT can be seen in Table 1. Where eligible, a research appointment is arranged for the following week, where a consent form is completed along with collection of blood samples and provision of an accelerometer (to capture intensity of physical activity) to wear continuously for the following week. All men are also provided with a pedometer (to measure daily step count), to wear for the 6-month duration of the trial. The data items that are being collected are listed in Table 2.

The men are randomised into both the nutritional and physical activity intervention arms of the trial and provided with instructions specific to their intervention allocation. They receive texts, emails and post relating to the trial interventions, including recipe ideas and motivational messages, as applicable to their allocated intervention, to encourage continuation of their trial arm intervention throughout the 6-month trial period. These contacts take place at 1, 2, 5, 8, 13, 15 and 18 weeks post-randomisation. They include gratitude for ongoing support of the research and a reminder of the importance of the data collected. Men are reminded of the changes they have been asked to make and the data they have been requested to record daily. Instructions are given of how to carry out the behaviour change, as well as being reminded of the potential benefits of the new behaviour, and men are informed that others similar to them carry out the intended behaviour. Message content was developed in line with the Theory of Planned Behaviour [32] (See Theoretical Underpinning below).

At 3 and 6 months following randomisation, the men attend a follow-up research appointment, where repeat questionnaires are completed. At the 6-month follow-up appointment, a blood sample is taken. For the final week of the trial, men wear an accelerometer to record the intensity of their physical activity.

We intend to recruit 100 men to the cohort, and of these, randomise at least 80 to the randomised controlled trial.

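### The exploratory analysis of change in activity and in fruit and vegetable intake is tied to adherence measures that have no scheduled value before randomisation

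*Protocol article*

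**What the plan says.** The Analysis plan section announces exploratory two-way ANOVAs, or non-parametric tests if needed, of "change in physical activity and fruit and vegetable consumption (as measured for adherence to the interventions". The words in parentheses send the reader back to the definition of adherence.

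Primary outcome measures gives that definition. For diet, "Adherence to the nutrition intervention will be assessed by participant self-report on the daily monitoring form". The fruit and vegetable item is a count: "for vegetable and fruit consumption, men are asked how many portions they consumed daily". On timing, "This form is completed daily by the participants for the duration of the 6-month intervention". For activity, the measure is "self-reported adherence to the recommended minimum 30 minutes of brisk walking five times per week during the 6-month intervention phase".

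Table 2 (under Initial recruitment phase) has a row for "Daily monitoring data Step count, record of fruit, vegetable, dairy and lycopene intake", with one timing mark, in the column for the intervention period. The pedometer row has the same single mark. The text on recruitment into the randomised trial agrees: "All men are also provided with a pedometer (to measure daily step count), to wear for the 6-month duration of the trial".

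**The concern.** A change score needs a starting value. The sentence names an outcome (change) and a source (the adherence measures), and the source has no value from before the intervention. The article is therefore not merely silent on a detail. It specifies a variable that cannot be built as change from baseline.

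An analyst who keeps to the named source can form a change only inside the intervention period, for example late against early diary weeks. Men receive their instructions at the start of that period. A man who takes up the behaviour at once and keeps it up would then show no change, and so would a control participant who alters nothing. At stake are between-arm comparisons of behaviour in a feasibility trial whose stated purpose is to inform a larger one.

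**Working it through.** **1. The plan's own figure.** The same paragraph of the Analysis plan states about 90 % power for a main effect of f = 0.4 with 80 men and alpha 0.05 in the 2 x 3 design. With six cells:

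- noncentrality = f² × N = 0.16 × 80 = 12.8
- error degrees of freedom = 80 − 6 = 74
- nutrition main effect (2 and 74 df): power 0.891
- physical activity main effect (1 and 74 df): power 0.942

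The stated figure is reproduced for nutrition and is slightly exceeded for activity. Because f is standardised to whatever outcome is analysed, these values stay the same for any instrument at the same f and N. The power statement is not in dispute.

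**2. Schedule of the measures.** From Table 2, except where noted:

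| Measure | Cohort baseline | True trial baseline | Intervention period | 3 months | 6 months |
|---|---|---|---|---|---|
| Daily monitoring form (nutrition adherence) | no | no | yes | no | no |
| Self-reported brisk walking (activity adherence; no row of its own, timing from Primary outcome measures) | no | no | yes | no | no |
| FFQ | yes | yes | no | yes | yes |
| Recent Physical Activity Questionnaire | yes | yes | no | yes | yes |
| Accelerometry | yes | yes | no | no | yes |

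The adherence measures have 0 scheduled values before randomisation. The two questionnaires have 2 each.

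**3. What a within-diary change would estimate.** The article does not describe such an analysis, so this step rests on assumptions. Suppose the intervention produces a sustained difference D between arms, control participants do not change, and a share u of the uptake is already present in the diary period used as reference. The contrast in change is then D − uD = (1 − u)D. The article gives no value for u, which could lie anywhere from 0 (nothing lost) to 1 (all of D lost). This shows the direction of the risk but not its size.

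**4. What a comparison of levels would estimate.** If the arms are compared on mean intake over the intervention period, with no change score, randomisation makes the contrast unbiased for D without any baseline value. The diary can therefore support a between-arm comparison, provided it is not called change.

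**5. The activity measure.** As defined, it is adherence to a walking instruction. Under Interventions, the comparison group is asked to continue at its usual level and receives no such instruction. Apart from the missing baseline, the measure is a poor outcome for comparing the two activity arms.

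**The case against.** The strongest reply is that this is loose drafting in a condensed article. The sentence is grammatically garbled, the analysis is labelled exploratory, and the choice of variable is something an analysis plan would commonly settle. The parenthesis might mean only the same behaviours, not the same instrument. For activity, the article names no instrument behind the self-report, so it is not shown to come from the diary.

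Some of this stands. The activity half is less certain as to instrument, although its timing is explicitly the intervention phase. The analysis is indeed exploratory. But the article does not leave the source open. It names one, and a later plan that follows the sentence would inherit the mismatch. If the looser reading was meant, the wording still points to the wrong place.

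Two stronger readings are tempting and are not supported:

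- *The trial has no baseline for diet or activity and cannot estimate change.* The FFQ, the activity questionnaire and accelerometry are all scheduled at both baselines. The Abstract lists change in diet and in general physical activity as secondary outcomes, and Secondary outcome measures extends this to all other data collected.
- *The contrast will be biased by half or more because change will be taken from the first diary days.* Nothing in the article says so. Any such percentage simply restates the assumed u in step 3 of the working.

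**Conclusion.** The point holds in a limited form. The source named for the exploratory change analyses has no value before randomisation, so change from baseline cannot be computed from it. A within-diary change could understate the difference between arms, by an amount that cannot be quantified from the article. The conclusion rests on reading the parenthesis as naming the measure, and on the timings in Primary outcome measures and Table 2. It is firmer for fruit and vegetables, where the form is named, than for activity.

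Severity is moderate to minor. The randomisation rate and the adherence rate, each reported as a percentage with a 95 % confidence interval, do not depend on this analysis. Nor does the stated power.

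**What to change.** In the Analysis plan, replace the reference to the adherence measures with named instruments that have a true trial baseline:

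- fruit and vegetables: the FFQ;
- physical activity: the Recent Physical Activity Questionnaire;
- accelerometry in addition, only if the baseline wear week is confirmed to precede the intervention. The article has the device worn in the week after the consent appointment and does not say whether randomisation waits for it.

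Compare arms on the 6-month value adjusted for the true trial baseline value, keeping the factorial structure. The adjustment is a recommendation. The mismatch itself is resolved once a source with a baseline is named.

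Keep the daily monitoring data for adherence. If they are also compared between arms, drop the word change, compare levels over the intervention period, and first confirm that all arms complete the same items.

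The cost is a few lines of wording and a little analysis work. No new data are needed, since both questionnaires are already scheduled at true trial baseline, 3 months and 6 months.
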